### Participant timeline {13}

The participant timeline is detailed in Fig. 1. The participant schedule of enrolment, interventions and assessments is detailed in Fig. 2 SPIRIT figure. Any new adult who attends a hearing assessment appointment at a participating adult hearing aid service during the 3-month recruitment period will be included in the trial. All patients who receive a hearing aid(s) will then follow the clinical pathway to which their audiology service has been randomised, as described in Section Trial design {8}. All patients who receive a hearing aid(s) will be invited to complete a research questionnaire 12 weeks after their hearing aid(s) fitting. If a patient completes their consent form and 12-week questionnaire, they will be sent another questionnaire at 12 months post-fitting for the collection of the primary outcome data. A subgroup of participants who provide consent to take part in a semi-structured interview will be contacted after 12 weeks of hearing aid(s) use.

**Fig. 2 Fig2:**
[figure not shown]
FAMOUS SPIRIT schedule of enrolment, interventions and assessments

### Sample size {14}

There are approximately 140 traditional NHS services (supplemented by some High Street providers funded to support the NHS) fitting hearing aids to 355,000 new adult users each year, so approximately 211 per service each month. We assume that 25% of participants will provide individual follow-up research data at 12 weeks post-fitting, with 80% of these providing primary outcome data (i.e. 20% of all patients enrolled in clinic). Since services will each recruit for 3 months, this will give an average cluster size for analysis of approximately 130 participants. The intra-class correlation coefficient (ICC) for the primary outcome is unknown, but based on published ICC data for a broad range of outcomes and settings, we assume it to be between 0.02 and 0.05 [22].

Our target treatment effect is a difference in mean hours of use per day of 1–1.5 h. With 90% statistical power, a 5% two-sided significance level, ICC = 0.02, a standard deviation = 5.5 [23] hours, and a target mean difference of 1 h, a total of 36 sites and 4680 participants are required for the analysis. Based on a 25% consent rate (at 12 weeks), a total of 23,400 patients need to be recruited, with 5850 participants consenting to follow-up data collection at 12 weeks post-fitting and 4680 providing primary outcome data at 12 months.

If the ICC is 0.05, the trial will have 90% power to detect a difference of 1.4 h (84 min), and 80% power for a difference of 1.2 h (72 min). There is an association between daily duration of hearing aid use and reported benefit, such that even a small effect of the intervention in increasing mean hours of hearing aid use could be clinically important. Our PPI contributors indicated that 60–90 min is a meaningful increase in usage.

Table 1 below shows the detectable differences in mean minutes of hearing aid usage at 80% and 90% power for ICCs ranging from 0.02 to 0.05 and coefficient of variation from 0.4 to 0.9.

**Table 1 Tab1:** Detectable differences in mean for minutes of hearing aid usage with varying power, intra-class correlation and coefficient of variation

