		**Intra-class correlation coefficient (ICC)**			
		0.02	0.03	0.04	0.05
**Coefficient of variation (CoV)**		90% power			
	0.4	60	70	79	86
	0.5	61	70	79	86
	0.6	61	71	80	87
	0.7	62	72	80	88
	0.8	64	73	81	89
	0.9	65	74	82	89
		80% power			
	0.4	52	61	68	74
	0.5	52	61	68	75
	0.6	53	61	69	75
	0.7	54	62	70	76
	0.8	55	63	70	77
	0.9	56	64	71	77

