## Assignment of interventions: allocation

### Sequence generation {16a}

Randomisation will take place at a cluster level (NHS audiology service) with a 1:1 allocation ratio to structured care or usual care, using stratified block randomisation (stratifying by tertile of site size determined by obtaining up-to-date figures on the number of new hearing-aid fittings per month directly from participating services before randomisation). The trial statistician will prepare a dummy randomisation list using Stata version 17 [24]. The trial database systems developer will modify the random seed to generate the real randomisation schedule. There is a second-level randomisation for the SWAT.

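### At ICC 0.05 the text's detectable differences (84 min at 90% power, 72 min at 80%) contradict Table 1 (86–89 and 74–77 min) and are slightly too favourable

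*Protocol article*

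**What the plan says.** Sample size {14} treats the ICC of the primary outcome as unknown and says "we assume it to be between 0.02 and 0.05". The main calculation is at the lower end: "With 90% statistical power, a 5% two-sided significance level, ICC = 0.02, a standard deviation = 5.5" h and a target difference of 1 h, leading to "a total of 36 sites and 4680 participants are required for the analysis". For the upper end, ICC 0.05, the text says "the trial will have 90% power to detect a difference of 1.4 h (84 min), and 80% power for a difference of 1.2 h", with 72 min in brackets after the second figure. It names no CoV for either figure.

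Table 1 follows directly and lists detectable differences in minutes by power, ICC and CoV. Its ICC 0.05 column reads, for CoV 0.4, 0.5, 0.6, 0.7, 0.8 and 0.9:

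- 90% power: 86, 86, 87, 88, 89, 89
- 80% power: 74, 75, 75, 76, 77, 77

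**The concern.** The sentence and the table describe one scenario in one unit and disagree in all 12 cells, each time with the sentence more favourable. The smallest tabulated values exceed the text by 2 min (86 against 84, 74 against 72) and the largest by 5 min (89 against 84, 77 against 72). For a detectable difference, a figure that is too small claims more power than the design has. Because the ICC is unknown, this sentence tells the reader what the trial can detect if the ICC lies at the top of the assumed range, so it should agree with the table that it introduces.

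**Working it through.** **Inputs.** All are from Sample size {14} except the allocation.

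- SD and target: "a standard deviation = 5.5 [23] hours, and a target mean difference of 1 h", so SD = 330 min and target = 60 min.
- Test: 5% two-sided, so z = 1.960. For 90% power add 1.282 (sum 3.242); for 80% add 0.842 (sum 2.802).
- Cluster size: "this will give an average cluster size for analysis of approximately 130 participants".
- 36 sites, "with a 1:1 allocation ratio to structured care or usual care" (Sequence generation {16a}), so 18 sites and 18 × 130 = 2340 participants per arm.
- Assumption: the CoV in Table 1 is that of cluster size. The article does not say so, but the table reproduces on that reading.

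**Step 1: reproduce the main calculation (ICC 0.02).**
Individually randomised n per arm = 2 × 3.242² × (330/60)² ≈ 636. Design effect = 1 + 129 × 0.02 = 3.58. 636 × 3.58 ≈ 2277 per arm, and 2 × 2277/130 = 35.03 clusters, rounded up to 36; 36 × 130 = 4680. This agrees with the plan.

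**Step 2: reproduce Table 1.**
SE = 330 × √(2 × DE/2340), with DE = [1 + 129 × ICC] / [1 − CoV² × L × (1 − L)] and L = 130 × ICC/(130 × ICC + 1 − ICC). This is the normal approximation for a mixed model with unequal clusters. It matches every cell of Table 1 to within 1 minute.

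At ICC 0.05: 1 + 129 × 0.05 = 7.45; L = 6.5/7.45 = 0.872; L(1 − L) = 0.111.

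| CoV | SE (min) | Detectable, 90% | Table 1 | Detectable, 80% | Table 1 |
|---|---|---|---|---|---|
| 0 (equal) | 26.3 | 85.4 | – | 73.8 | – |
| 0.4 | 26.6 | 86.1 | 86 | 74.4 | 74 |
| 0.9 | 27.6 | 89.5 | 89 | 77.3 | 77 |

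Equal clusters are the most favourable case, and even they need more than 84 and 72 min. No choice of CoV rescues the text.

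**Step 3: power at the figures in the text.** Power = Φ(d/SE − 1.96).

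| CoV | Power for 84 min | Power for 72 min |
|---|---|---|
| 0 (equal) | 89.1% | 78.1% |
| 0.4 | 88.5% | 77.3% |
| 0.9 | 86.1% | 74.2% |

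Over the tabulated CoVs the shortfall is 1.5 to 3.9 points against 90% and 2.7 to 5.8 points against 80%.

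**Step 4: a check that uses Table 1 alone.** Taking SE from the printed cells (86/3.242 and 89/3.242; 74/2.802 and 77/2.802) gives power for 84 min of 88.6% to 86.4%, and for 72 min of 77.8% to 74.5%. The result therefore does not depend on the variance formula in Step 2.

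**Step 5: other methods.** A t reference with 34 df lowers power further (87.3% and 75.7% with equal clusters). The more conservative design effect 1 + ((CoV² + 1) × 130 − 1) × ICC gives larger detectable differences (91.1 min at 90% power and CoV 0.4) and does not reproduce Table 1. Neither brings the result closer to the text.

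**Step 6: probable origin.** At CoV 0.4, 86.1/60 = 1.43 h (1.435) and 74.4/60 = 1.24 h. To one decimal these are 1.4 h and 1.2 h, and 1.4 × 60 = 84, 1.2 × 60 = 72.

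**The case against.** The best defence is that the hour figures are ordinary rounding. To one decimal, 1.4 h and 1.2 h agree with the CoV 0.4 and 0.5 results (86.1 and 86.6 min; 74.4 and 74.8 min), and CoV 0.4 is also the row that gives the 60 min of the main calculation. On this view only the bracketed minutes are wrong, and the right values stand just below. That stands as an explanation and limits the weight of the point. It does not remove it: the text prints whole minutes beside a table in whole minutes, and the two disagree.

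It is also fair to say that the gap is small. Moving the ICC from 0.02 to 0.05 shifts the detectable difference by 26 min at CoV 0.4 and 90% power (60 to 86), against 2 to 5 min here. The larger power shortfalls belong to CoV 0.9, which the text does not attach to its figures. Clinic recruitment ended in March 2025, so the design can no longer change on this account. All of that stands.

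A reader might infer that the headline of 60 min at 90% power and ICC 0.02 is likewise wrong, since only the CoV 0.4 row shows 60. The documents do not support that. Table 1 openly shows 60 to 65 min by CoV, and the text makes no contrary claim. Nor does the article use the ICC 0.05 sentence to argue that the design is robust, and with no SAP or report shown there is no evidence that the wrong minutes have been carried anywhere.

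**Conclusion.** The point holds as a minor error in stated power. At ICC 0.05 the minute figures in the text contradict Table 1 and are 2 to 5 min too favourable. Under the plan's inputs, power over the tabulated CoVs is 86.1–88.5% for 84 min, not 90%, and 74.2–77.3% for 72 min, not 80%. This rests on the normal approximation, the stated SD, mean cluster size and site number, and CoV read as that of cluster size; Table 1 reproduces on the same basis. The rounding explanation is likely but is an inference.

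It does not show that the trial is underpowered or wrongly sized. The 36 sites and 4680 participants come from ICC 0.02 and 60 min and reproduce. Every Table 1 value at ICC 0.05 (74 to 89 min) stays within the 60 to 90 min that the public contributors regarded as meaningful, so the article's conclusion about the upper end of the ICC range is unchanged.

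**What to change.** Replace the sentence with the Table 1 values: at ICC 0.05 the trial has 90% power for a difference of 86 to 89 min and 80% power for 74 to 77 min, depending on a CoV of 0.4 to 0.9. If hours are kept, give them to two decimals (1.43 to 1.48 h and 1.23 to 1.28 h) so that they convert back to the table.

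The cost is one sentence and slightly less favourable figures. Table 1, the sample size, the number of sites and the analysis stay as they are.

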		**Intra-class correlation coefficient (ICC)**			
		0.02	0.03	0.04	0.05
**Coefficient of variation (CoV)**		90% power			
	0.4	60	70	79	86
	0.5	61	70	79	86
	0.6	61	71	80	87
	0.7	62	72	80	88
	0.8	64	73	81	89
	0.9	65	74	82	89
		80% power			
	0.4	52	61	68	74
	0.5	52	61	68	75
	0.6	53	61	69	75
	0.7	54	62	70	76
	0.8	55	63	70	77
	0.9	56	64	71	77

### Recruitment {15}

Patients will be informed and reminded about FAMOUS during their clinic visits and told to expect the 12-week questionnaire pack in the post. To supplement this information, and to ensure the trial remains as inclusive as possible, an animated video about the trial and what patients should expect will be available in four key languages spoken in the UK (English, Polish, Punjabi and Welsh). Links to the videos are provided (on trial posters and information cards) and on the trial website. Patients will receive a single telephone call to remind them to complete their 12-week questionnaire. As a ‘thank you’ gesture, all participants will be given a £10 shopping voucher for completing research outcomes at the 12-week and 12-month time points.

## Assignment of interventions: allocation

### Sequence generation {16a}

Randomisation will take place at a cluster level (NHS audiology service) with a 1:1 allocation ratio to structured care or usual care, using stratified block randomisation (stratifying by tertile of site size determined by obtaining up-to-date figures on the number of new hearing-aid fittings per month directly from participating services before randomisation). The trial statistician will prepare a dummy randomisation list using Stata version 17 [24]. The trial database systems developer will modify the random seed to generate the real randomisation schedule. There is a second-level randomisation for the SWAT.

### Concealment mechanism {16b}

NHS audiology services will be randomised after confirmation of their participation via a centrally held concealed allocation list hosted by the Nottingham Clinical Trials Unit (NCTU). The Trial Manager (or authorised designee) will access the NCTU web-based randomisation system to obtain the allocation for the site.

### Implementation {16c}

Site teams will be notified of their randomisation allocation via email prior to Site Initiation Visit (SIV), and subsequently trained according to their randomisation allocation. Site teams include clinical hearing professionals within the audiology department and research and development staff who will be responsible for delivery of the trial protocol.

## Assignment of interventions: blinding

### Who will be blinded {17a}

It is not possible to blind the intervention.

### Procedure for unblinding if needed {17b}

N/A.

## Data collection and management

### Plans for assessment and collection of outcomes {18a}

#### Routine medical data

Baseline clinical data will be extracted from Auditbase, the audiology electronic health record and patient management system used by NHS audiology services across the UK. Recruiting sites will install a custom script that will produce a report containing the baseline pseudonymised clinical data required for the trial. This includes demographics (age, sex and ethnicity), hearing assessment (audiogram information, real-ear verification of the prescription), hearing aid prescription (model and manufacturer, dates of issue) and the frequency and format of clinic appointments. All data is collected at baseline, during the assessment and fitting appointments, except for follow-up clinic appointments over the first year of hearing aid use; this data is collected each time a new report is run and provided to the NCTU.

#### PROMs

After 12 weeks of hearing aid use, eligible patients will be sent a paper questionnaire pack by their local audiology team. This will include a consent form and a questionnaire booklet for participants to complete themselves, either on paper or electronically, which can be accessed via a quick-response (QR) code. Paper questionnaires will be returned by post to the trial team at the NCTU, using pre-paid stamped addressed envelopes supplied within the questionnaire pack. Participants who consent to be contacted again at 12 months post-fitting will be sent a second questionnaire pack via their preferred method (email or post) as specified on their consent form. Data collection forms can be found in the electronic Trial Master File (TMF).

#### Qualitative trial data

Participants, hearing professionals and service managers will be contacted directly by telephone to arrange interviews. Interviews will be conducted via telephone or video call, and audio recorded, anonymised, and transcribed for analysis.

### Plans to promote participant retention and complete follow-up {18b}

During clinic appointments hearing professionals will encourage patients to complete and return their 12-week questionnaire. They will be informed that they will receive a £10 shopping voucher if they complete and return their questionnaires. When completing their consent form at 12 weeks post-fitting, participants can opt in to receive up to three text reminders to complete their 12-month questionnaire. Participants who do not return their 12-month questionnaire after three reminders have been sent will receive a telephone call from the trial team, and they will be asked for the primary outcome measure.

In order to maintain participant interest, updates about trial activity and relevant information about hearing will be posted on a trial website and shared via social media.

### Data management {19}

All trial baseline data are part of core clinical data held within Auditbase. The Principal Investigator (PI) or delegated hearing professional will be responsible for running the FAMOUS custom report within Auditbase to extract the routine data required for the trial. A member of the site study team will then upload the baseline clinical data reports into the FAMOUS Research Electronic Data Capture (REDCap) database monthly.

Routine clinical data from Auditbase is required from first patient first visit (hearing assessment) up to 12 months post-fitting of the last patient enrolled (last patient first visit + 12 months). Patient data collected from Auditbase will be pseudo-anonymised using Auditbase identifier (ID) and Site ID so that the patient cannot be identified by anyone outside of their direct care team. At 12 weeks post-hearing aid fitting, the questionnaire pack sent to patients will be labelled with the same Auditbase ID and Site ID number. Upon receipt of the returned consent form and questionnaire pack, the two datasets will be linked using the Auditbase ID and Site ID. Data linkage is verified by ensuring the date of birth provided by the participant matches the month and year of birth provided in the Auditbase reports. Any discrepancies are queried with the site staff. Patient identifiable contact information will be collected in the 12-week questionnaire pack with consent, and this will then be used by the FAMOUS trial team to re-contact the participant at 12 months post hearing aid fitting and for the qualitative interviews, where applicable.

Paper questionnaires returned to the FAMOUS trial team at NCTU will be entered into the FAMOUS REDCap database by a member of the NCTU data management team, and quality reviewed by a separate member of the team. Decisions on how to treat anomalous data will be made by members of the TMG blinded to allocations and documented in the Data Management Plan (DMP) and/or Statistical Analysis Plan (SAP) (where required).

### Confidentiality {27}

The FAMOUS REDCap database will be held in a secure server hosted by the University of Nottingham.

Pseudo-anonymised routine clinical data will be accessed only by the FAMOUS trial team for the purposes of monitoring and data linkage. The FAMOUS data and programming teams are responsible for linking routine clinical data with questionnaire data. The anonymised dataset will be saved on password-protected machines only accessible to members of the trial team at NCTU. Identifiable information about participants (such as address data for questionnaires) will be held in a separate area to the pseudo-anonymised linked dataset with access restricted to those involved in follow-up only, as authorised by the Chief Investigator (CI). Personal data recorded on all documents will be regarded as strictly confidential and is handled and stored in accordance with the Data Protection Act 2018. Identifiable patient contact details will be deleted prior to database lock and will not be included in the study analysis.

### Plans for collection, laboratory evaluation and storage of biological specimens for genetic or molecular analysis in this trial/future use {33}

Not applicable.

## Statistical methods

### Statistical methods for primary and secondary outcomes {20a}

The analysis and reporting of the trial will be in accordance with Consolidated Standards of Reporting Trials (CONSORT) guidelines for cluster trials [25]. A full SAP has been developed and will be finalised prior to database lock and agreed with the Trial Steering Committee (TSC).

The primary approach to between-group comparative analyses will be by intention-to-treat (i.e. including all patients according to randomised allocation regardless of site adherence to trial allocation). The main analysis for the primary outcome will include all randomised participants who consent to provide follow-up data at 12 weeks or 12 months. Where appropriate, imputation will be used so that all randomised participants may be included in a sensitivity analysis.

Descriptive statistics will be used to describe balance between the groups at baseline at site- and patient-level [26], including the characteristics of those that do and do not provide consent to follow-up. The primary comparative analysis will employ a mixed effects linear regression model to compare the hours of use at 12 months in each group, adjusting for factors balanced at randomisation and participant-level characteristics (e.g. age, sex, socio-economic status), where technically possible. The model will include a random effect to adjust for clustering within sites. The comparison will be presented as a difference in means, along with a corresponding 95% confidence interval.

Secondary outcomes will be analysed using appropriate multilevel regression models dependent on data type (e.g. binary, continuous, time-to-event), adjusting for factors balanced at randomisation and participant-level characteristics (e.g. age, sex, socio-economic status), where technically possible. The model will include a random effect to adjust for clustering within sites.

Appropriate interaction terms will be included in the primary regression analyses to conduct subgroup analyses according to the severity of hearing loss at baseline, sex, index of multiple deprivation, and unilateral/bilateral hearing aid fitting, but this analysis will be regarded as exploratory as the study is not powered to detect interactions. Interpretation of any subgroup effects will be based on the treatment-subgroup interaction and the corresponding 95% confidence interval.

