### Trial design {8}

FAMOUS is a multi-centre, two-arm parallel-group CRCT with integral internal pilot, economic and process evaluations. During a 3-month recruitment phase at each participating NHS adult hearing service, the service’s trial allocation (structured care or usual care) will be adopted as their sole clinical follow-up plan. All patients attending the participating services for a hearing assessment will be treated in line with the service’s trial allocation and will subsequently be invited to complete patient-reported outcome measures (PROMs) 12 weeks after their hearing aids have been individually prescribed, fitted and verified. Those who consent and provide outcomes at 12 weeks after fitting will be re-contacted at 12 months for collection of the primary outcome. The trial design is detailed in Fig. 1.

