### Methods in analysis to handle protocol non-adherence and any statistical methods to handle missing data {20c}

As described in Section Statistical methods for primary and secondary outcomes {20a}, imputation will be used so that all randomised participants may be included in a sensitivity analysis where appropriate.

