## Trial status

At the time of submission of manuscript revisions (August 2025), 11,844 patients have been included in the trial, with 8,134 eligible to receive their first questionnaire pack at 12 weeks post-hearing aid(s) fitting. 1,711 (21%) participants have consented and provided questionnaire responses at 12 weeks post-fitting. 759 (73%) have provided primary outcome data. Clinic recruitment ended on 7 March 2025, with final primary outcomes to be collected around May 2026.

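### The primary analysis is labelled intention-to-treat but includes only patients who consent 12 weeks after fitting, about 21% of those sent a questionnaire

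*Protocol article*

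**What the plan says.** Under Statistical methods for primary and secondary outcomes {20a}, the protocol article describes the primary approach as intention-to-treat, "including all patients according to randomised allocation regardless of site adherence to trial allocation". The next sentence defines the set used: "The main analysis for the primary outcome will include all randomised participants who consent to provide follow-up data at 12 weeks or 12 months".

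Patients enter the trial at the assessment appointment without individual consent (Who will take informed consent? {26a}). Consent and the first outcomes are requested 12 weeks after fitting (PROMs, under {18a}). Under Trial design {8}: "Those who consent and provide outcomes at 12 weeks after fitting will be re-contacted at 12 months for collection of the primary outcome". Participant timeline {13} says the same.

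For patients outside this set, {20a} says: "Where appropriate, imputation will be used so that all randomised participants may be included in a sensitivity analysis". The missing-data section {20c} repeats it: "imputation will be used so that all randomised participants may be included in a sensitivity analysis where appropriate". Section {20a} also plans adjustment for participant characteristics and a descriptive account of baseline balance, "including the characteristics of those that do and do not provide consent to follow-up".

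Trial status reports, for August 2025, 11,844 patients included, 8,134 eligible for the 12-week pack, and "1,711 (21%) participants have consented" and responded. Primary outcome data are held for 759 (73%).

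**The concern.** In a cluster trial that enrols everyone at assessment, the randomised population is every eligible patient at the allocated services. The main analysis instead uses those who choose to respond after receiving the allocated care, in a trial that cannot be blinded. Randomisation does not protect a comparison within a group formed in this way.

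The outcome is hours of use, and use may well influence who returns a questionnaire about hearing aids. If that influence is the same in both arms, the responder means shift together and the difference is unaffected. If it differs by arm, the difference is biased.

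The design offers a route to such a difference. Under {18b}, "During clinic appointments hearing professionals will encourage patients to complete and return their 12-week questionnaire". Under Intervention description {11a}, structured-care patients with low use or significant problems at the 7-day call are invited back to clinic. Exposure to prompting can therefore vary with both arm and use. An unqualified intention-to-treat label would lead readers to credit the result with a protection it lacks.

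**Working it through.** **1. The plan's own figures.** Sample size {14} assumes 25% consent and 80% retention: 23,400 × 0.25 = 5,850, and 5,850 × 0.80 = 4,680. Both match the text. Analysis of about 20% of enrolled patients was therefore intended from the start. The 21% in Trial status also reproduces: 1,711 / 8,134 = 21.0%.

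**2. Share of the randomised population.**
- Of all included: 1,711 / 11,844 = 14.4%. This denominator contains 11,844 − 8,134 = 3,710 patients not eligible for the pack. The article does not break them down, but those who declined a fitting are among the patients whose routine data are collected.
- If 73% retention holds for all consenters: 1,711 × 0.73 = 1,249 primary outcomes, which is 15.4% of 8,134 and 10.5% of 11,844. About 85% of outcomes among questionnaire-eligible patients would then be unobserved.

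**3. The order of events.** Structured care schedules steps at assessment, at fitting, at 7 days and at 6 weeks. Usual care offers a follow-up at 6–12 weeks. The consent request comes at 12 weeks, so the scheduled contacts are largely over in both arms. Section {20a} also allows for consent at 12 months, but {8} and {13} give no 12-month contact without a 12-week response. The 12-week response is thus the gate to the analysis.

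**4. Illustration with no true effect.**
- From the Background: 20% of people fitted do not use their aids and 30% use them only some of the time. That leaves 50%, so p = (0.2, 0.3, 0.5).
- Assumed: hours h = (0, 4, 10), and response rates r in the order non-users, part-users, full users.
- Responder mean = Σ(h·p·r) / Σ(p·r). The mean over everyone is 0.3 × 4 + 0.5 × 10 = 6.2 h in both arms.
- Usual care, r = (0.14, 0.20, 0.245): (0.240 + 1.225) / (0.028 + 0.060 + 0.1225) = 1.465 / 0.2105 = 6.96 h.
- Structured care, r = (0.10, 0.20, 0.26): (0.240 + 1.300) / (0.020 + 0.060 + 0.130) = 1.540 / 0.210 = 7.33 h.
- Difference: 7.33 − 6.96 = 0.37 h, or 22 min, with overall response 21.05% and 21.0%.

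Each arm overstates its own mean (by 0.76 h and 1.13 h), and only the gap between these becomes bias. Swapping the two response patterns gives −0.37 h. Using one pattern in both arms gives zero.

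**5. A second model.** Assume hours are normal with SD 5.5 h (the plan's value) and correlated ρ with a latent tendency to consent. With consent proportions p₁ and p₀, bias = ρ × 5.5 × [φ(z₁)/p₁ − φ(z₀)/p₀], where z is the normal point with upper tail p. Absolute bias for ρ from 0.1 to 0.5:

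| Consent by arm | Bias (min) |
|---|---|
| 13% v 15% | 2.4 to 12.0 |
| 12% v 16% | 4.8 to 24.1 |
| 20% v 22% | 1.8 to 8.9 |
| 19% v 23% | 3.6 to 17.8 |

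With ρ positive, the arm with the lower response shows the higher responder mean. Equal rates and the same mechanism in both arms give no bias.

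**The case against.** The restriction is stated openly in the sentence after the label, and it has a reason. The Confidentiality Advisory Group advised that explicit consent was required, and {26a} argues that avoiding consent in clinic reduces selection by staff. The pack, the reminder call and the voucher are described without distinction by arm. Usual care also includes a follow-up visit, so only the 7-day contact and any recall that follows are clearly extra. With some 85% of outcomes unobserved, caution about imputation is defensible. The imputation model belongs in an SAP that is not shown. All of this stands, and none of it makes the consenting set the randomised population.

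A reader might also infer four stronger points that the article does not support:
- That selection alone could produce an effect as large as the target. The illustrations shown reach 22 to 24 minutes, and the 22-minute example needs non-user response to fall from 14% to 10%, a relative drop of 29%.
- That the bias favours structured care. Recalling low users to clinic could raise their response and pull the result towards no difference.
- That imputation is the only provision. Covariate adjustment and a comparison of consenters with non-consenters are planned.
- That the imputation will assume data missing at random. The article does not say.

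**Conclusion.** The concern holds as a mislabelled primary population combined with an uncommitted analysis of the full one. The conflict between the label and the analysed set is on the page, and entry to that set follows randomisation and most of the allocated care. The analysed share so far is 21% of questionnaire-eligible patients, or 14.4% of those included; both are August 2025 figures.

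The possible bias is a material fraction of the 1 h target: 22 minutes in the worked example, and about 2 to 24 minutes in the second model. Those sizes rest on assumed hours, response rates and correlations. They show what could happen, not what has happened. The article gives no response rates by arm, so neither the presence nor the direction of bias can be judged from it. The planned adjustment and description are useful but cannot recover patients who never respond.

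**What to change.** Describe the main analysis as as-allocated among consenting responders, in place of unqualified intention-to-treat. Before database lock, commit without condition to two supporting analyses of fitted patients:

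- (a) response weighting or multiple imputation with arm-specific models, using the Auditbase data held on all eligible patients (age, sex, ethnicity, audiogram, prescription, appointments and site);
- (b) an arm-specific delta-adjusted (tipping-point) analysis, showing how far non-responders' hours would have to differ between arms to change the conclusion.

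Intervention description {11a} says the intervention aims to raise uptake as well as use, so being fitted may itself depend on arm. Report fitting rates by arm among all included patients. Show response rates and responder profiles by arm beside the primary result.

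The consent process need not change and no new data are needed. The cost is SAP wording, analysis time and supporting results with wide uncertainty, because most outcomes are unobserved. The article says the SAP will be finalised before database lock and expects the last primary outcomes around May 2026, so there is room to make the change.
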